### Protocol

#### Testing procedure

All participants will attend four baseline sessions, each one week apart. Session one will last approximately 20 minutes, while the remaining sessions will last approximately 60 minutes. At the first session, held during the evening, participants will be provided with an accelerometer and instructed in the correct measurement protocol. During session two, to be held early in the morning, health measures (anthropometry, blood pressure and blood chemistry) will be taken and participants will complete a dietary questionnaire. At the end of this session, participants will be provided with, and instructed in, the use of a Salivette saliva sampling kit. Session three, held during the afternoon, will comprise the completion of a further three questionnaires assessing psychological wellbeing, sweet-drink intake and general health/demographics. All questionnaires will be self-administered using a computer-based survey system. Two three-minute walking tests will also be completed. Session four, performed at baseline only, provides an information session for the participants about the details of the intervention, designed separately for Intervention and Control groups. The Control group will be instructed on the importance of participating in regular physical activity as per the Australian Physical Activity Guidelines
[10], how to setup and use their pedometer (Yamax DW700; Yamasa Tokei Keiki Co. Ltd., Tokyo, Japan) and tips for incorporating physical activity into daily life. The Intervention group, in addition to the information provided to the Control group, will be shown how to use the REACH website, including how to log their steps and other information. Measures will be repeated following the 12-weeks of the intervention period, and at 6-months and 12-months follow-up (i.e. 3-months and 9-months from end of the intervention). Participants will be recruited from three intervention regions: the Riverland; the Copper Coast (Upper Yorke Peninsula); and the Lower Yorke Peninsula. In each location, testing sessions will be provided in four different towns on different days. This is to minimise participant burden by providing a number of opportunities to participate around their usual schedule and reduce distances needed to travel. Testing will begin in the Riverland, followed by the Copper Coast and then the Lower Yorke Peninsula. Testing in the second and third regions will begin during the information session (session four) of the preceding region.

#### Intervention protocol

The REACH intervention involves three key components, the REACH website, weekly step goals and ongoing progress support provided in the form of telephone interviews. The specifics of, and access to, these three key attributes are dependent on group allocation. Participants in both groups will use a pedometer to monitor the number of steps taken each day. Those in the Control group will be provided with a standard logbook to record their steps. The Intervention group will be provided access to the REACH website. The website allows the participant to record their steps, which are then depicted on a graph, to provide feedback to the participant in an easy to read visual format. In addition to steps taken, participants will also record their affective state (how they are feeling) and ratings of perceived exertion (RPE). Intervention participants will input these on the REACH website, while control participants will make note in their logbooks. The REACH website also provides an online forum where participants can share their experiences and tips with others in the program and provide peer support. A virtual notice board will collate information on community events and services, walking groups and other relevant region-specific information. This aspect of the website is designed to provide ready access to supervised and socially focussed opportunities to be physically active in their local communities. The website will also provide ready access to healthy eating guidelines based on the recommendations of The Australian Guide to Healthy Eating
[28].

Ongoing progress support phone calls will be provided to the Intervention group only. These phone calls will occur in weeks two, three, four, six, eight and twelve. The purpose of gradually reducing contact with the participant is to foster a milieu of independence and increased self-efficacy within the participant. These phone calls will be approximately 15 minutes in length and will cover aspects related to progress, website use, perceived barriers, injury/illness and tips for increasing physical activity through incorporation into daily routines. The Control group will receive one phone call during week two to ensure they understand the requirements of the study, but will not receive any additional progress phone calls thereafter.

#### Step goals

For the Intervention group, personalised step goals will be created using individuals’ RPE, affect and ability to achieve their previous week’s goals. RPE is determined using Borg’s
[29] 6–20 Ratings of Perceived Exertion (RPE) scale which serves to numerically quantify the perceived effort, strain, discomfort and/or fatigue experienced during physical activity by the individual undertaking it. RPE is a widely used construct, having been previously used to prescribe target exercise intensities in both healthy adults
[30, 31] and clinical populations
[32–35]. Previous research has suggested that RPE may be beneficial in populations where maximal exertion is contraindicated
[36]. Affective state (i.e. feeling good/bad) has been shown to significantly influence exercise behaviour and motivation
[37]. Participants will rate their daily affective state (i.e. how they feel [good or bad]) when they get out of bed on an 11-point Likert scale ranging from +5 (‘very good’) to -5 (‘very bad’)
[38].

Researchers on the REACH team will use these inputs (daily steps, RPE and daily affect) to generate individually tailored step goals for the following week. Participants are encouraged to maintain an exertion between RPE-11 (light) and RPE-13 (somewhat hard) on the RPE scale, the ‘bandwidth’ within which people have reported the most positive response to exercise
[39–41]. Step goals will be provided in the form of a ‘target range’. The first week will serve as a baseline from which to set the first goals, with a 5-10% increase per week in step goals. If participants do not meet their previous week’s step goals on most days, the goals for the preceding week will not change.

Step goals for the Control group will be generic across all control group participants. Step goals will start at 5,000 to 6,000 steps in week one and progress in weekly increments of 500 steps until reaching the recommended 10,500 to 11,500 steps
[5, 12] in week 12 of the intervention.

### Outcome measures

The primary outcomes are daily minutes spent participating in sedentary, light intensity and moderate-to-vigorous intensity physical activity. The mean daily activity intensity will also be assessed. To objectively measure these outcomes, participants will wear a tri-axial wrist-worn accelerometer (GENEActiv; Activinsights Ltd, Cambridgeshire, United Kingdom), on their non-dominant wrist, for a period of seven consecutive days (five week days and two weekend days). Matthews and colleagues
[42] argue that seven days of monitoring provides sufficient data to achieve intra-class correlations of greater than 80%, and ensures the inclusion of both week day and weekend day behaviours. The GENEActiv’s design is unobtrusive and water proof, minimising the need for removal and therefore maximizing compliance with continued wear over the sampling period. Output data will be analysed using cut-points previously established by Esliger and colleagues
[43] from 60-second epochs using a custom-made algorithm in Microsoft Excel. Non-wear time will be assessed automatically using a custom-made algorithm. Monitors are to be worn for no fewer than sixteen hours in a day for the day to be classed as valid. A minimum of three valid week days and one valid weekend days will be required (four days in total) for the overall monitoring period to be acceptable. The GENEActiv shows high technical reliability, with intra- and inter-device variability of 1.8% and 2.4%, respectively
[43], while its ability to discriminate between different intensities of physical activity is similar to other devices extensively used in physical activity research (GENEActiv: 0.90-0.93 [area under the curve] vs Actigraph GT1M: 0.94 vs RT3: 0.95)
[43].

Secondary outcomes include:

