**Methods/Design:**

This is a randomised controlled trial. The intervention is 12-weeks with a 12-month follow-up. Participants will be insufficiently active, aged 18 to 70 years and randomly assigned to either Control or Intervention group. Participants receive a pedometer, but only the Intervention group will receive access to the purpose built REACH website where they will report steps taken, affect and ratings of perceived exertion during daily walking. These variables will be used to establish individualised step goals for increasing walking. Control participants will receive a paper diary to record their variables and generic incremental step goals.

The primary outcome measures are time spent in sedentary, light and moderate-to-vigorous intensity physical activity, measured by accelerometry. Secondary outcomes include 1) health measures (anthropometric and physiological), 2) psychological well-being, 3) diet quality, and 4) correlates of physical activity (exercise self-efficacy and physical activity environments). Measures will be collected at baseline, post-intervention, 6-month and 12-month follow-up.

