#### Statistical plan

Data will be collated and manipulated using Microsoft Excel 2010 (Microsoft Corporation, Redmond, WA). Statistical analyses will be performed using STATA Data Analysis and Statistical Software version 12 (StataCorp LP, College Station, TX) and SPSS version 21 (IBM corp., Armonk, NY). Significance levels will be set at α = 0.05. Distributions of all variables will be assessed using the Shapiro-Wilk test, with appropriate normalization procedures applied where required. Independent samples t-tests will be performed on baseline measures to test for differences in demographic outcomes. Change scores for all outcomes will be calculated and compared between randomisation groups using parametric or non-parametric analyses as appropriate for the data distributions. Random effects mixed modelling will be used with time (0, 12, 26 and 52 weeks) and group allocation (Intervention and Control) as the fixed factors. A time by group interaction term will be used to formally test the aims of the study.

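### Three unranked primary activity outcomes are tested at 0.05 with no success rule, alpha allocation or primary visit; if any one may count as success, the false-positive chance is about 10–14%, not 5%

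*Protocol article*

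**What the plan says.** The article names its primary outcomes twice, and both lists agree. The Abstract says: "The primary outcome measures are time spent in sedentary, light and moderate-to-vigorous intensity physical activity, measured by accelerometry". Outcome measures says: "The primary outcomes are daily minutes spent participating in sedentary, light intensity and moderate-to-vigorous intensity physical activity". Neither place ranks the three or says whether one, two or all must favour the intervention. Outcome measures then adds, before the secondary list begins: "The mean daily activity intensity will also be assessed".

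On timing, the Abstract says: "Measures will be collected at baseline, post-intervention, 6-month and 12-month follow-up". No visit is singled out.

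On analysis, the Statistical plan gives one level for everything: "Significance levels will be set at α = 0.05". It describes the model thus: "Random effects mixed modelling will be used with time (0, 12, 26 and 52 weeks) and group allocation (Intervention and Control) as the fixed factors". The test that carries the aims is this: "A time by group interaction term will be used to formally test the aims of the study". The same paragraph also plans a second between-group analysis, with no visit attached: "Change scores for all outcomes will be calculated and compared between randomisation groups".

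**The concern.** Three results could each be reported as the trial's primary finding, each judged at the full 0.05. Unless a rule says how they combine, a reader cannot tell what a positive trial is, and the error rate of the overall claim is not fixed at 5%.

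The three outcomes are also parts of the same day. Minutes gained in one category are largely minutes lost in another, so two significant results may be one shift seen twice. This correlation lowers the inflation but does not remove it.

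The formal test adds a second difficulty. With time as a factor at four levels, the interaction asks whether the groups' profiles differ anywhere over 52 weeks. A significant result does not say at which visit they differ or in which direction. The programme lasts 12 weeks, and the natural question is whether activity was higher when it ended. The omnibus test does not answer that by itself, and the visit used to describe the effect could be picked once the data are known.

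**Working it through.** **Inputs from the article.** Three primary outcomes (Abstract; Outcome measures). Alpha 0.05, taken as two-sided because the article does not say. Time points 0, 12, 26 and 52 weeks, two groups, interaction as formal test (Statistical plan). 106 per group, d = 0.5, 80% power, R² = 0.5 (Sample size).

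**Inputs assumed.** All correlations and standard deviations among outcomes; the article gives none.

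**The plan's own figure.** The article states no family-wise error rate, so there is none to reproduce. The sample size does not follow from a simple two-group comparison: n = 2(1.960 + 0.842)²/0.5² = 62.8, so 63 per group, or 32 if R² = 0.5 halves the variance, against the stated 106. The calculation behind 106 is therefore unknown. Below, 106 and d = 0.5 serve only as the plan's own scale.

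**1. Any one outcome counts, outcomes independent.** 1 − 0.95³ = 0.143, and 14.3/5 = 2.9 times nominal.

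**2. Any one outcome counts, outcomes correlated.**

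| Assumed structure | Chance of ≥1 false positive | Multiple of 5% |
|---|---|---|
| Sedentary = −(light + MVPA), SDs 60 and 30 min, light–MVPA correlation 0 to 0.5, with or without 40 min of added noise; one test per outcome | 9.6–12.2% | 1.9–2.4 |
| Correlations sedentary–light −0.85, sedentary–MVPA −0.60, light–MVPA 0.20; 3-df test per outcome | 11.4% | 2.3 |
| Equal correlation 0.5; 3-df test per outcome | 12.8% | 2.6 |
| Equal correlation 0.7; 3-df test per outcome | 11.2% | 2.2 |
| Equal correlation 0.9; 3-df test per outcome | 8.6% | 1.7 |

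The rate is above 5% in every case tried. Whether each outcome gets a 1-df or a 3-df test hardly matters: the second row gives 11.2% with 1 df.

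**3. All three outcomes required.** A false claim then needs every test to be significant, including one whose null hypothesis is true, so its probability is at most 5%. There is no inflation.

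**4. Omnibus test against a named contrast.** The interaction has (4 − 1) × (2 − 1) = 3 df. At 106 per group and d = 0.5, the noncentrality is 106 × 0.5²/2 = 13.25, with square root 3.64.

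- 1 df: Φ(3.64 − 1.96) = Φ(1.68) = 0.95.
- 3 df: P(χ²₃ with noncentrality 13.25 > 7.81) = 0.88.

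This takes the effect to lie wholly in one contrast, so that both tests have the same noncentrality. It is a simple two-group approximation, not a calculation for the mixed model.

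**5. Price of control.** Holm's strictest step is 0.05/3 = 0.0167, critical value 2.394. Power there is Φ(3.64 − 2.394) = Φ(1.246) = 0.89, against 0.95 at 0.05.

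**The case against.** The strongest reply is that this is a condensed article. A multiplicity procedure and the exact primary contrast are often left to the analysis plan, and a general 0.05 is compatible with Holm across three outcomes. That is a fair limit: an unseen plan may already settle the matter. It does not dispose of the point, because the article itself fixes three equal primary outcomes, the significance level and the formal test. Followed as written, with any one outcome counting, these give the rates above.

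It is also true that no any-one-wins rule is stated. The inflation is conditional on that reading.

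An interaction over 52 weeks also fits the article's interest in a sustained response. This stands as a reason to keep the later visits, though not as an answer to whether activity rose by week 12.

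Four stronger readings are tempting and are not supported:

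- **Visits multiply the tests.** A reader might count three outcomes at three follow-ups and reach 22–27% (visit correlation 0.6), or about five times nominal. The formal test is one interaction per outcome covering all visits. The change-score comparisons could be run visit by visit, but the article does not say so and does not make them the formal test.
- **Mean intensity is a fourth primary outcome.** This would give 1 − 0.95⁴ = 18.5% under independence. Both lists of primary outcomes contain only three items.
- **The error exceeds a stated rate.** The article gives a nominal alpha only, so the comparison is with 5%.
- **The omnibus test drops power to about 64%.** That figure starts from a contrast with exactly 80% power on 1 df. At the article's 106 per group and d = 0.5, the same calculation gives about 88%.

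**Conclusion.** The point holds, conditionally and at moderate size. The article leaves open how three primary outcomes combine and which visit decides. If any one significant outcome may be called success, the chance of at least one false positive is about 10–12% when sedentary time mirrors activity and 14.3% under independence. That is roughly 2–3 times nominal, though very high correlation would bring it somewhat below 2. The correlated figures rest on assumed standard deviations and correlations. If all three outcomes must be positive, there is no inflation.

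The second part rests on time being a four-level factor, which the listing of time points as a fixed factor supports. The interaction then does not locate the effect at week 12. The power it gives up for a single-contrast effect is real but modest, about 88% against 95%.

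This should be settled in the plan. It does not invalidate the design.

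**What to change.** In the Statistical plan, before outcome data are analysed:

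- Name the week-12 between-group difference in change from baseline, estimated from the planned mixed model (1 df), as the primary contrast for each of sedentary, light and moderate-to-vigorous minutes.
- Control the three at 0.05 overall with Holm's procedure, or with a fixed sequence whose order is written down in advance, and state which result counts as success.
- Label mean daily intensity and the week-26 and week-52 contrasts as secondary.
- State that the separate change-score comparisons are supportive.

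Making moderate-to-vigorous minutes the sole primary outcome would also resolve the multiplicity, but that is the sponsor's choice and is not required.

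The cost is a change of wording and a little power: about 89% instead of 95% per outcome at alpha 0.0167, with 106 per group and d = 0.5 in a simple two-group comparison. On those inputs, no participants need be added. The later follow-ups carry less formal weight, which matters because sustained change is among the article's interests; they would still be estimated and reported.

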#### Anthropometry

The following anthropometric measures will be taken: standing stretch stature; body weight and composition (Tanita BC-418; Tanita Corp., Tokyo, Japan); and waist and hip circumferences (Lufkin Executive Thinline 2 m W606pm; Apex Tool Group, LLC, Sparks, MD). All anthropometric measures will be taken in accordance with the International Standards for Anthropometric Assessment
[44] by the same research personnel at all time periods. Body composition, expressed as percentage body-fat, will be assessed using single frequency (50 Hz) bioelectrical impedance analysis scales (Tanita BC-418). Assessment of body composition by the Tanita BC-418 shows strong correlation with measures by dual-energy x-ray absorptiometry (Pearson’s r = 0.87) with excellent test-retest reliability (intra- and inter-day coefficients of variability of 0.8-1.4% and 2.3-3.7%, respectively)
[45]. A minimum of two measures will be taken for each outcome. A third measure will be required if initial measures differ by ≥1%. Final measures will be reported as the mean of two measures, or if a third was required, the median of all three.

#### Blood pressure

Resting blood pressure will be measured in a seated position using an automated sphygmomanometer (GE Carescape V100; GE Healthcare, Little Chalfont, United Kingdom) after participants have been rested for a period of five minutes. A minimum of two measures will be taken, with at least two minutes rest, with the cuff removed, between measures. Additional measures will be required if either systolic or diastolic pressures differ by >5 mmHg, to a maximum of four measures. Final resting blood pressure will be reported as the mean of the two closest measures.

#### Blood chemistry

Blood cholesterol, triglycerides and fasting plasma glucose will be assessed from an overnight fasted (minimum eight-hours) fingertip blood sample. Samples will be collected by research personnel experienced in fingertip blood sampling techniques and analysed on-site using Cholestech LDX (Alere Inc., Waltham, MA) technology. The Cholestech LDX analyser shows excellent agreement with laboratory analyses
[46] and has been validated as an alternative to laboratory analyses for assessing the presence of metabolic syndrome
[47].

#### Psychological measures

Psychological well-being will be assessed using the short-form Depression, Anxiety and Stress Scale (DASS-21). The DASS-21 is a self-administered questionnaire and comprises 21 items that are separated into three sub-scales representing three domains of psychological well-being: depression; anxiety; and psychological stress. Each sub-scale can be represented by a numerical score or categorised into five categories: normal; mild; moderate; severe; and extremely severe, as per the recommendations of Lovibond & Lovibond
[48]. The DASS-21 has been validated for use in non-clinical populations as a tool for assessing symptomatology and has extensive empirical backing for validity and reliability, boasting Cronbach alpha coefficients of 0.88, 0.82 and 0.93 for the depression, anxiety and stress sub-scales, respectively
[49].

Salivary cortisol will be assessed as a biomarker of psychological distress. There is emerging evidence that perturbations to cortisol’s underlying circadian rhythm may occur as a result of psychological or emotional distress. Seven saliva samples will be collected from each participant on a single week-day using Salivette collection devices (Sarstedt, Nümbrecht, Germany). Sample 1 (S1) is to be collected immediately on awakening, at 30 minutes and 60 minutes post-awakening (S2 and S3, respectively). In light of anecdotal evidence suggesting considerable difference in daily routines in rural populations, daily milestones rather than strict time points will be used to collect the remaining samples. These will be mid-morning (halfway between S3 and lunch), 30 minutes before lunch, 30 minutes before dinner and immediately prior to going to bed. Participants will be asked to abstain from smoking, consuming food or fluids (except water), brushing their teeth and strenuous physical activity for at least one hour prior to providing the sample. Participants will record the exact time of each sample on a log sheet. There is considerable evidence to suggest the use of hormonal contraceptives, hormone replacement therapies and cortisone based medications may alter cortisol regulation
[50]. As such information regarding these factors will be collected by a research assistant from participants returning their samples. Analyses of samples will be performed using a standard enzyme-linked immunosorbent assay protocol (ELISA; Salimetrics LLC., State College, PA) at the University of South Australia. Parameters of the cortisol rhythm will be quantified based on recommendations from the literature
[51, 52].

